### 6.3 Special Instructions and Definitions of Evaluations

All clinical and laboratory information required by this protocol is to be present in the source documents. Sites must refer to the Source Document Guidelines on the DAIDS Web site for information about what must be included in the source document: <http://www.niaid.nih.gov/labsandresources/resources/daidsclinrsrch/documents/sourcedocappndx.pdf>.

All stated evaluations are to be recorded on the case report forms (CRFs) and keyed into the database unless otherwise specified.

6.3.1 Documentation of HIV Status

HIV-1 infection will be documented as described in section 4.1.3.

If the confirmatory test of the HIV status reported at screening is negative, the participant must discontinue study treatment and be followed as described in section 6.2.4, above, to monitor any toxicity.

- - 1. Documentation of CM Status

CM must be documented either by a positive CSF cryptococcal culture **or** a **locally licensed** positive CSF India ink preparation, or a positive CSF cryptococcal antigen latex agglutination test within 7 days prior to entry. **A positive CSF India ink or cryptococcal antigen latex agglutination test received from a referring laboratory must be confirmed within 5 days after study entry by CSF antigen testing from an approved laboratory or with a positive entry CSF culture by Day 5.**

**If the confirmatory test of CM is negative, the participant must be discontinued from study treatment immediately, referred immediately to his/her health care provider for appropriate management, and be followed as described in section 6.2.4, above, to monitor for any toxicity.**

6.3.3 Medical/Medication History

Medical History

The medical history must include all AIDS-defining diagnoses using WHO criteria (see the A5225/HiFLAC MOPS or <http://www.who.int/hiv/pub/prev_care/en/arvrevision2003en.pdf>) for the participant’s lifetime and all diagnoses identified by the ACTG criteria for clinical events and other diagnoses ([http://www.fstrf.org](http://www.fstrf.org/)) for the 3 months prior to study entry. For current ACTG criteria, refer to the appendix identified in the study CRF. Any allergies to any medications and their formulations must be recorded on the CRF. Record diagnoses on the CRF and key within 48 hours.

Medication History

A medication history, limited to ARVs, opportunistic infection (OI) treatment and prophylaxis, and TB and antifungal therapy taken in a participant’s lifetime, must be present in CRFs, and must include actual or estimated start and stop dates. In addition, all medications taken within 14 days prior to study entry should be recorded on the CRF.

Current alternative therapies and traditional treatments are to be recorded as yes/no on the CRF. If answered yes, the alternative therapy or traditional treatment will be listed in the source documents only.

6.3.4 Length of Hospitalization

The date of hospital/clinic admission for the current episode of CM must be recorded at entry. Ongoing hospitalization and the date of discharge, if it falls at or before week 24, must also be recorded. In addition, subsequent re-admission to hospital for treatment of CM must be recorded, along with date of discharge, if prior to week 24.

6.3.5 Concomitant Medications

Study staff are expected to work closely with hospital staff during any participant’s hospitalization to ensure that prohibited concomitant medications are avoided if possible, and to ensure on a daily basis that all medications provided to a participant have been documented.

The Concomitant Medications section of the A5225 MOPS includes links to websites that can be consulted for information about known or possible drug-drug interactions.

Any OI treatment and/or prophylaxis, and TB and antifungal therapy other than ampho B or study-provided fluconazole that was started or stopped since the last visit must be recorded on the CRFs. For 5-fluorocytosine **or fluconazole that is administered with ampho B**, the dose must be recorded on the CRFs also.

Current alternative therapies and traditional treatments are to be recorded as yes/no on the CRF. If answered yes, the alternative therapy or traditional treatment will be listed in the source documents only.

6.3.6 ART (Initiation and Modification)

All modifications to ART must be recorded on the CRF. Modifications include initiation as well as any changes in dose or formulation, interruptions of 2 or more consecutive days, or discontinuations for any reason.

Although initiation of ART prior to week 4 is discouraged for participants taking high dose fluconazole, participants who initiate ART that does not contain NVP prior to Step 3 may remain on study. Participants who initiate NVP while taking high dose fluconazole (ie, at a dose higher than 400 mg daily) must be discontinued from study treatment.

6.3.7 Study Treatment Modifications

All modifications to ampho B-based regimens or to study-provided fluconazole, including initial doses, participant-initiated and/or protocol-mandated interruptions of 2 or more consecutive days, any modifications, and any permanent discontinuation of treatment will be recorded on the CRFs at each visit and keyed within 48 hours. Participant-initiated and protocol-mandated interruptions include both inadvertent and deliberate interruptions of the ampho B-based regimens or of study-provided fluconazole.

6.3.8 Complete Physical Examination

A complete physical examination is required as noted in the SoE.

In addition to all evaluations listed under Clinical Assessments below, a complete physical exam will include a neurological exam as well as axillary or oral temperature (Centigrade or Fahrenheit), pulse, blood pressure, respiratory rate, and examination of the following: head, eyes, ears, nose, and throat (HEENT), neck, chest, heart, abdomen, extremities, and skin. The neurological examination will include cranial nerve assessments with emphasis on cranial nerves II, III, IV, V, VI, and VIII, evaluation of the presence of meningeal irritation, a fundoscopic examination, a functional assessment using the A5225/HiFLAC study-specific neurology CRF, and an overall Karnofsky performance status assessment.

At entry, current functional assessment will be determined. Prior functional assessment will be reported for a time within approximately 6 weeks prior to the onset of the current illness. Information may be provided by a friend or family member if the participant cannot recall or otherwise provide the requested information.

6.3.9 Clinical Assessments

At the visits indicated in the SoE, clinical assessments should be conducted and should be driven by any previously identified or new signs or symptoms or diagnoses that the subject has experienced since the previous visit.

Vital Signs

Vital signs (temperature, pulse, respiratory rate, and blood pressure) must be recorded on the CRFs.

Signs and Symptoms

At entry, all signs and symptoms occurring within 3 days prior to entry must be recorded and keyed within 48 hours. In Stage 1, Steps 1 and 2, beginning on Day 1, all Grade ≥ 3 signs, symptoms, and toxicities, and those that lead to a change in treatment, regardless of grade, must be recorded and keyed within 48 hours. For Stage 1, Steps 3 and 4, and in all of Stage 2, regardless of step, all Grade ≥ 3 signs, symptoms, and toxicities, and those that lead to a change in treatment, regardless of grade, must be recorded.

In addition, in Stages 1 and 2, the identification of symptoms that lead to the evaluations described under section 6.2.3 must be brought to the attention of the study core team via e-mail within 2 weeks after the site’s becoming aware of these symptoms.

Sites must refer to the DAIDS Table for Grading the Severity of Adult and Pediatric Adverse Events, Version 1.0, dated December 2004, which can be found on the DAIDS RSC Web site: [http://rsc.tech-res.com/safetyandpharmacovigilance/.](http://rsc.tech-res.com/safetyandpharmacovigilance/.  ) .

Diagnoses

All diagnoses identified by the ACTG criteria for clinical events and other diseases must be recorded and keyed within 48 hours.

Classification of Progression of Symptoms

In addition, using data generated from evaluations conducted as described under 6.2.3, investigators will classify progression of symptoms as one of the following:

1) microbiological failure (i.e., positive CSF culture)

2) complication of CM (e.g., obstructive hydrocephalus or vascular complications such as venous or arterial thrombosis)

3) IRIS to CM causing increased inflammation after exposure to ART

4) a new CNS OI (e.g., toxoplasmosis, PML, CNS lymphoma)

5) possibly related to CM but mechanism indeterminate

6) other defined complication unrelated to CM.

6.3.10 Height and Weight

Height and weight must be measured and recorded at entry. If weight cannot be measured, an estimated weight, based on recent records or according to site investigator judgment, may be used (a notation that the weight has been estimated must be included in these cases). The participant’s actual weight must be measured directly as soon as possible; if actual weight is obtained within 4 days after entry, dose adjustments may be made based on this weight, as warranted.

The same height measurement will be used for all PK visits for participants who were at least 21 years old at study entry; for all others, height must be measured and recorded at each PK visit.

After entry, weight must be measured and recorded as indicated on the SoE.

6.3.11 Glasgow Coma Scale

Neurological assessments using the Glasgow Coma Scale (which can be found in section 7 of the A5225/HiFLAC MOPS) must be performed at every study visit beginning at study entry and must be recorded.

6.3.12 ECG

Resting ECG results, including heart rate and measured QT interval, must be recorded as indicated in the SoE, sections 6.1. The QT interval should ideally be taken from limb lead II. See section 7.2 for clinical management directions for participants with prolonged QT interval on study. Note that when recording QT interval at visits after entry, the site is responsible for documenting any change relative to the baseline value.

6.3.13 Hematology and Chemistries

At entry, all screening and entry laboratory values must be recorded and keyed within 48 hours. In Stage 1, Step 1, beginning on Day 1, and in Stage 1, Step 2, all Grade  2laboratory toxicities, any laboratory toxicities that lead to a change in treatment, regardless of grade, and all estimated creatinine clearance values must be recorded and keyed within 48 hours. In Stage 1, Steps 3 and 4, and in all of Stage 2, regardless of step, all Grade  2laboratory toxicities, any laboratory toxicity that leads to a change in treatment, and all estimated creatinine clearance values must be recorded.

Sites must refer to the DAIDS Table for Grading the Severity of Adult and Pediatric Adverse Events, Version 1.0, dated December 2004, which can be found on the DAIDS RSC Web site: [http://rsc.tech-res.com/safetyandpharmacovigilance/.](http://rsc.tech-res.com/safetyandpharmacovigilance/.  )

Hematology

Hemoglobin, hematocrit, white blood cell count (WBC), differential WBC, platelets and absolute neutrophil count (ANC).

Because of the frequent occurrence of ampho B toxicities, the tests listed above should be performed twice weekly while ampho B is administered.

Blood Chemistries

Glucose, electrolytes (sodium, potassium, chloride, bicarbonate), total bilirubin, AST (SGOT), ALT (SGPT), albumin, alkaline phosphatase, and creatinine.

Because of the frequent occurrence of toxic side effects, serum potassium, bicarbonate, creatinine, and serum magnesium level should be performed twice weekly while ampho B is administered.

Estimated Creatinine Clearance

Creatinine clearance should be estimated each time that a creatinine level is determined (unless creatinine clearance is measured directly).

To estimate creatinine clearance, use the following method of Cockcroft and Gault:

For men: {(140 - age in years) x (body weight in kg)} ÷ (serum creatinine in
mg/dL x 72).

For women: use the same calculation as for men, then multiply the result by 0.85.

A calculator is available at the Data Management Center Web site at <https://www.fstrf.org/ACTG/>.

6.3.14 Pregnancy Test

For women of reproductive potential: Serum or urine -HCG (the upper limit for sensitivity of a urine test is 50 mIU/mL; tests that are more sensitive, i.e., with lower detectable limits, are acceptable) must be performed as indicated on the SoE. Beginning at entry, results of any pregnancy tests must be recorded on the CRF.

Women who become pregnant on study must discontinue study treatment immediately. These women may remain on study, off study treatment, after signing a pregnancy consent form, or may elect to go off study. Regardless of their decision, these women should seek CM treatment outside the study. See sections 6.2.4 and 7.6 for additional instructions. Pregnancy outcome data will be collected and recorded in the woman’s source documents and on the CRF even though this may occur after study end.

6.3.15 CD4+ Cell Counts

CD4+ cell counts (both absolute and subset percentage counts) should be performed at the same laboratory, if possible, throughout the study. Within the U.S., laboratories must be CLIA certified. Outside the U.S., laboratories must be ACTG approved. Because of the diurnal variation in CD4+ cell counts, samples for each participant should be obtained consistently in either the morning or the afternoon throughout the study.

CD4+ counts must be obtained from all participants at the visits indicated in the SoE. Note that if CD4 counts are obtained within 72 hours prior to study entry, a repeat of this determination is not required at study entry.

6.3.16 Plasma HIV-1 RNA

The HIV-1 RNA quantitations must be performed real time using any approved HIV RNA quantitation assay. Within the U.S., laboratories must be CLIA certified and have DAIDS approval. Outside the U.S., laboratories must be participating in the VQA and be DAIDS approved. HIV-1 RNA data will be reported on the CRF when they are not reported through the Laboratory Data Management System (LDMS).

HIV-1 RNA values must be obtained from all participants at the time points indicated in the SoE. Note that if a sample for HIV-1 RNA is obtained within 72 hours prior to study entry, a repeat of this determination is not required at study entry.

6.3.17 Lumbar Puncture/Opening Pressure

Throughout the study, all lumbar punctures (LPs), including those performed as part of clinical care (eg, for diagnosis, monitoring, or for the relief of intracranial pressure) should be recorded on the CRF, along with the opening pressure. Section 9 of the A5225/HiFLAC MOPS contains instructions for the preferred method for performing LPs on study.

6.3.18 CSF Cryptococcal Antigen

Detection of CSF cryptococcal antigen will be performed at screening or entry using a latex-Cryptococcus antigen detection system **and should be positive within after study entry or the participant is to be discontinued (see section 6.2.4). A negative CSF antigen titer by latex agglutination will not exclude the participant if the entry CSF culture is positive for *C. neoformans*.** A 2-fold titer will be reported.

6.3.19 CSF Glucose, Protein, & Cell Counts

Each time an LP is performed for collection of CSF, glucose and protein determinations and cell counts (indicating numbers of red blood cells and numbers of white blood cells only) must be performed real time on the CSF.

6.3.20 Stored CSF Sample

Each time an LP is performed for collection of CSF, a CSF sample must be stored.

6.3.21 Mandatory CSF Cultures

**To remain in the study, participants’ qualifying CSF culture must be positive by Day 4 if a confirmatory CSF cryptococcal antigen titer by latex agglutination is not positive by Day 5.**

During screening or at study entry and again at week 2, a CSF sample for culture must be obtained from all participants. Each time a CSF sample for culture is required, both a qualitative and a quantitative culture must be performed (see instructions in section 2 of the A5225/HiFLAC MOPS).

Additional CSF samples may be required based on participants’ response to study treatment. See section 6.3.22, below.

CSF collection and cultures must be performed at the Progression of Symptoms visit.

Wherever possible, CNS imaging should be performed at the same time that CSF samples are obtained for evaluation of progression of symptoms.

6.3.22 Possible CSF Cultures

Beginning at week 4 and continuing through week 10 (ie, at weeks 4, 6, 8, and 10), CSF must be collected and both qualitative and quantitative cultures must be performed for all participants whose previous quantitative culture was positive.

CSF collections should be performed on participants who prematurely discontinue study treatment only as clinically indicated; there are no subsequent study-required cultures for these participants.

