- Cohort Set 1: fluconazole 1200 mg daily or ampho B-based regimen. Once the safety data for the last participant enrolled in Cohort 1 has been reported, reviewed, and found to be acceptable, Cohort 2 may be opened. Cohort 1 was opened to accrual on **x/x/x, and closed to accrual on x/x/2011**.
- Cohort Set 2: fluconazole 1600 mg daily or ampho B-based regimen. Once the safety data for the last participant enrolled in Cohort 2 has been reported, reviewed, and found to be acceptable, Cohort 3 may be opened. **Cohort 2 was opened to accrual on 10/7/2011 and closed to accrual on 6/x/2012.**
- Cohort Set 3: fluconazole 2000 mg daily or ampho B-based regimen. **Cohort 3 was opened to accrual on 7/x/2012 and closed to accrual on 8/x/2013.**

Fluconazole

Participants randomized to receive fluconazole will enter Step 1 and receive the assigned induction dose, adjusted for weight, for a minimum of 4 weeks and a maximum of 10 weeks.

In addition to the cerebrospinal fluid (CSF) samples collected at screening or entry, CSF samples will be collected at week 2 and every 2 weeks through week 10 until a negative culture is obtained. If a negative culture is obtained prior to week 10 (i.e., negative culture results are available at or before week 8 from a sample collected at least 2 weeks previously), the participant will enter Step 3 and will receive fluconazole 400 mg daily [or 600 mg daily if receiving rifampin (RIF)] until week 10. It is possible that a participant will not enter Step 3.

At week 10, all participants will enter Step 4 and receive fluconazole 200 mg daily through week 24. Note that participants randomized to fluconazole will not enter Step 2, which is described below.

Ampho B

Participants randomized to receive an ampho B-based regimen in Step 1 will receive amphotericin B deoxycholate at a dose of 0.7-1.0 mg/kg daily as part of the local standard of care (SoC) for approximately 2 weeks. At each site, the daily ampho B dose will be the same for each cohort.

In addition to the CSF samples collected for culture at screening or entry, CSF samples will be collected for culture at week 2 and again every 2 weeks through week 10 until a negative culture is obtained.

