The primary efficacy outcome measure is the change in quantitative CSF culture for cryptococcus. During screening or at entry, CSF samples for culture will be collected from all participants. At week 2, CSF samples will again be collected from all participants and will be cultured. Additional CSF samples will be collected and cultured at weeks 4, 6, 8, and 10, until a negative culture following 2 weeks of incubation is obtained. Treatment failure for any participant is defined as a week 10 CSF culture (which is read by or at week 12) that is positive for *C. neoformans*.

If a week 10 CSF culture is positive (by or at week 12), participants may discontinue study treatment and be treated according to local standard practice, at the discretion of the site investigator. Participants who discontinue study treatment prematurely should be encouraged to remain on study, off study treatment and should be encouraged to return for the week 24 visit.

PK samples will be obtained at specified time points from all participants enrolled in fluconazole induction cohorts (see section 10.0 for sampling information). Plasma, urine, serum, and CSF samples will be collected from all participants and stored for retrospective evaluation of novel diagnostic methodologies (collection schedule is presented in section 6.1).

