4.2.**6** Known allergy, sensitivity to, or intolerance of fluconazole or other imidazole or triazole compounds, or to ampho B or other components of the standard of care ampho-B based regimen.

4.2.**7** History of clinically significant cardiac disease, in opinion of site investigator, including symptoms of ischemia, coronary artery disease, congestive heart failure, or arrhythmia.

4.2.**8** ECG (electrocardiogram) with QTc interval greater than 450 msec within 7 days prior to study entry.

4.2.**9** History of CNS disorder (excluding mood disorders) or concurrent CNS disorder(s) that, in the opinion of the investigator, would interfere with assessment of efficacy (e.g., ability to perform CSF sampling) such as lymphoma, neurocysticercosis, or toxoplasmosis.

4.2.**10** Receipt of investigational drug therapy within 30 days prior to study entry without prior approval of the A5225/HiFLAC core team.

4.2.1**1** Active drug or alcohol use, dependence, or other conditions that in the opinion of the site investigator would jeopardize the safety of a participant in the study or would render the person unable to comply with the study plan.

### 4.3 Inclusion Criteria – Step 2

4.3.1 Randomization to an ampho B-based regimen in Step 1.

4.3.2 Receipt of at least one dose of ampho B-based regimen in Step 1.

4.3.3 Premature discontinuation of ampho B in response to the occurrence of any treatment-limiting toxicity, as described in section 5 of the A5225/HiFLAC MOPS.

### 4.4 Exclusion Criteria – Step 2

4.4.1 Receipt of fluconazole monotherapy in Step 1.

4.4.2 Receipt of ≥8.4 mg/kg ampho B.

4.4.3 At or beyond Day 17 in Step 1.

### 4.5 Inclusion Criteria - Step 3

4.5.1 For participants in Step 1 who are currently receiving study-provided fluconazole, with no plans to discontinue study treatment, a negative CSF culture after 2 weeks incubation from a sample obtained at or before week 6 (days 35-49).

4.5.2 For participants in Step 1 who are currently receiving an ampho B-based regimen or alternative treatment, completion of approximately 2 weeks of treatment.

NOTE: The total amount of ampho B received by a participant is expected to be approximately 8.4 mg/kg.

4.5.3 For participants in Step 2 who are currently receiving study-provided fluconazole, with no plans to discontinue study treatment, negative CSF culture after 2 weeks incubation from a sample obtained at or before week 6 (day 35-49).

### 4.6 Exclusion Criteria – Step 3

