6.2.2 On-Study Evaluations

Entry

On-study evaluations are performed only after a participant is enrolled into the study. However, the following evaluations do not need to be repeated at entry if performed within 72 hours prior to entry: CD4 cell count, plasma HIV-1 RNA, LP with opening pressure recorded, CSF cryptococcal antigen test, CSF cultures initiated (quantitative and qualitative), CSF analyses, and stored CSF sample. Storage of a cryptococcal isolate from CSF collected at screening or entry is sufficient.

Participants must begin study-assigned treatment within 72 hours after entry, however, initiation of study-assigned treatment within 24 hours after entry is strongly encouraged.

Post- Entry

The visit schedule through day 7 should be based on the first day of treatment (day 1 = first day after first dose of fluconazole or ampho B-based regimen), not solely on the date of enrollment. The visits listed for Days 4 through 7 should be completed ± 1 day of those time points as indicated in the SoE, section 6.1.2 and 6.1.3.

The week 2 visit should occur on day 14, but may be completed 12-17 days after initiation of study treatment.

The weeks 4-10 visits should occur on the week noted in the SoE, but may be completed ± 3 days as indicated in the SoE, sections 6.1.2 and 6.1.3. The week 24 visit may be completed ±7 days of that week, as indicated in sections 6.1.2 and 6.1.3. Note that for participants whose previous CSF culture was positive, at least 14 days must elapse between visits.

Step 1 (Induction)

Participants are expected to remain on Step 1 from 2 to 10 weeks depending on the treatment to which they are randomized and their response to that treatment. Participants randomized to ampho B will register to Step 3 after approximately 2 weeks of ampho B treatment. Some participants taking ampho B may register to Step 2 (see below) before entering Step 3.

Participants randomized to fluconazole will remain in Step 1 until week 10 or until a CSF culture is negative, whichever is earlier.

Step 2 (Induction Following Amphotericin B Deoxycholate Intolerance)

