Participants in ampho B-based induction cohorts who experience a treatment-limiting toxicity may either remain in Step 1 and receive alternative treatment, if available, or may enroll in the induction following ampho B intolerance step (Step 2) and will receive 800 mg daily fluconazole or the maximum locally approved dose. Each site will be expected to identify the daily fluconazole dose that it will administer to its participants.

Step 3 (Consolidation)

Participants who are taking **study-provided** fluconazole in Step 1 or Step 2 may enroll in the consolidation step (Step 3) if they have a negative CSF culture documented by week 8. It is possible that some participants will enter Step 4 without enrolling in Step 3. Participants randomized to ampho B in Step 1 who do not enter Step 2, are expected to enter Step 3 after approximately 2 weeks, regardless of culture outcomes.

Participants in Step 3 will receive fluconazole at a dose of 400 mg daily until week 10. Participants in Step 3 who are taking rifampin, however, will receive fluconazole at a dose of 600 mg daily.

Step 4 (Maintenance)

At week 10, all participants currently on study treatment are expected to enroll in the maintenance step (Step 4) and receive fluconazole at a dose of 200 mg daily through study end.

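### Section 6.3.22 ties further CSF sampling to the quantitative culture alone, so a participant whose qualitative culture still grows has no required later sample, and the step-down criteria do not say which culture counts

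*Protocol*

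**What the plan says.** On what is cultured, 6.3.21 states that for every required CSF sample "both a qualitative and a quantitative culture must be performed".

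On when sampling continues, the protocol has two kinds of rule:
- 6.3.22, on the visits from week 4 to week 10, states: "CSF must be collected and both qualitative and quantitative cultures must be performed for all participants whose previous quantitative culture was positive". The qualitative result is not part of this trigger.
- The Schema: "CSF samples will be collected at week 2 and every 2 weeks through week 10 until a negative culture is obtained". Section 3.0 has sampling go on "until a negative culture following 2 weeks of incubation is obtained". The schedules in 6.1.2 and 6.1.3 likewise run until the previous culture is negative. None of these names the type of culture.

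On when the dose is reduced, 6.2.2 states: "Participants randomized to fluconazole will remain in Step 1 until week 10 or until a CSF culture is negative, whichever is earlier". It adds that those given study-provided fluconazole, whether in Step 1 or in Step 2, "may enroll in the consolidation step (Step 3) if they have a negative CSF culture documented by week 8". The Step 3 criteria 4.5.1 and 4.5.3 ask for a CSF culture that is negative after two weeks of incubation, from a sample taken no later than week 6. The type is again not stated. Step 3 means 400 mg daily, or 600 mg with rifampin.

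On failure, the Schema and 3.0 define it as a positive culture of the week-10 sample. The part of 5.1.1 on mycological failure at week 10 uses the most recent CSF culture.

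**The concern.** The two cultures of one sample can disagree. The protocol text shown neither defines a negative culture for that case nor says which result governs, and the one rule that names a type names only the quantitative culture.

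Ascertainment is at stake first. Both culture results are a primary outcome (9.2.1.2), time to CSF sterility appears in objective 1.3.4, culture negativity is used for the sample size in 9.3.2, and clearance before week 10 is an analysis outcome in 9.5.2. A participant who leaves required sampling with a growing qualitative culture has no later required sample to settle any of these, nor a week-10 sample on which to judge failure.

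Treatment is at stake second. Sites could reasonably read the same discordant result differently and keep participants on high-dose induction for different lengths of time within one arm.

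**Working it through.** There is no protocol figure to reproduce. The main check compares the rules for one discordant case: a week-2 sample with a negative quantitative and a growing qualitative culture, in a participant on study-provided fluconazole in Step 1.

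**Sampling**
- Under 6.3.22, the previous quantitative culture was negative, so no CSF is required at week 4 or later.
- Under the Schema, 3.0 and 6.1.2, sampling stops if the quantitative result counts as the negative culture. It continues if both must be negative.
- For failure under the Schema and 3.0, 6.3.22 requires no week-10 sample, so the definition cannot be applied. Under 5.1.1, the most recent culture is still the week-2 one, and whether it is positive depends on which of the two is read.

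**Step-down (day of sample plus 14 days of incubation)**
- If the quantitative result is enough: 14 + 14 = day 28.
- If both must be negative and sampling continues: clearance at week 4 gives 28 + 14 = day 42; clearance at week 6 gives 42 + 14 = day 56.
- If both must be negative but the site takes only the CSF that 6.3.22 requires: clearance is never documented and induction runs to week 10, day 70.
- Difference from day 28: 14, 28 or, at the extreme, 42 days at the induction dose instead of 400 mg.

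**Who is affected.** Culture-dependent step-down concerns participants on study-provided fluconazole in Step 1 (4.5.1) or Step 2 (4.5.3). Under 6.2.2, ampho B participants who do not enter Step 2 move to Step 3 at about two weeks whatever the culture shows, so for them only the sampling is affected.

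**Illustrative frequency.** The protocol gives an example EFA of -0.30 with s.d. 0.15 log10 CFU/mL/day, and about -0.42 as a detectable alternative (9.3.1). The rest is assumed: mean baseline 4.5, 5.0 or 5.5 log10 CFU/mL with s.d. 1.0; 0.1-0.5 mL plated for the quantitative culture (vq); 0.5-2 mL used for the qualitative culture (vl); Poisson counts; s.d. 0.15 at every EFA; and every participant sampled at week 2.

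With c = 10^(baseline + 14 × EFA), P(discordant) = E[exp(-c·vq) × (1 - exp(-c·vl))], integrated over baseline and EFA. The s.d. of log10 c is √(1.0² + (14 × 0.15)²) = √5.41 = 2.33.

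| Mean EFA | P(discordant), min to max | × 24 per Stage 2 arm |
| --- | --- | --- |
| -0.10 | 0.011 to 0.101 | 0.3 to 2.4 |
| -0.20 | 0.025 to 0.175 | 0.6 to 4.2 |
| -0.30 | 0.042 to 0.217 | 1.0 to 5.2 |
| -0.42 | 0.043 to 0.214 | 1.0 to 5.1 |

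For EFA -0.10 to -0.30 the minimum is at baseline 5.5 with vq = vl = 0.5 mL, and the maximum at baseline 4.5 with vq = 0.1 and vl = 2 mL. At -0.42 the two baselines change places.

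**The case against.** Several objections carry weight.

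- **A reader might infer that 6.3.22 itself lowers the dose.** It does not. It sets which collections are mandatory; step-down is governed by 4.5.1, 4.5.3 and 6.2.2. A sample that still grows Cryptococcus is not naturally called culture-negative, so early step-down needs a permissive reading. That reading is allowed by the wording but not required by it.
- **6.3.22 is a minimum and forbids no lumbar puncture.** A site can satisfy every section by sampling on while either culture grows. The day-70 case needs a site that demands two negatives yet takes no further CSF, so it is an extreme. The objection does not remove the conflict over what is required.
- **The manual of operations is not shown.** Its section 2, to which 6.3.21 refers for the cultures, may say how discordant results are read. Even so, the trigger is written in the protocol and names one culture.
- **The frequency is assumed, and the higher figures fit fluconazole poorly.** In the 2.1.2 table, -0.31 belongs to ampho B alone and -0.30 to -0.39 to ampho B with fluconazole. Section 2.2 expects week-2 sterility to be unlikely to match ampho B. The -0.10 to -0.20 rows are the safer illustration. Section 9.3.1 also allows for up to 15% very early deaths, so fewer than 24 per arm would be sampled. Section 5.1 describes Stage 1 as completed, so the fix cannot change its participants.
- **A reader might infer that the 97% in 2.2 (participants negative at 2 weeks who stayed negative on 400 mg) is shown not to cover a quantitative-only negative.** That would join the reference-list credit of the cited 1997 trial to the ACTG, among others, with the remark in 2.2 that earlier ACTG-sponsored trials did not use quantitative CSF cultures. The documents do not state how that trial cultured CSF, and its induction was ampho B, so the point does not rest on this.
- **The clinical effect may be modest.** All fluconazole participants are planned to have at least four weeks of high dose, and a culture is mandatory if symptoms progress. This limits the treatment concern but not the loss of ascertainment.

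**Conclusion.** The point holds as a badly fixed sampling rule. Two cultures are required on each sample, only the quantitative one triggers the next sample in 6.3.22, and the other sections use an undefined negative culture. For a discordant participant, clearance, time to CSF sterility and week-10 failure may not be ascertained, and step-down to 400 mg from about day 28 with yeast still growing is permitted though not required. If both cultures had to be negative, step-down after a discordant week-2 sample would come 14 or 28 days later with continued sampling.

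How often this happens cannot be derived from the protocol. Roughly 1-22% at week 2 over EFA -0.10 to -0.42, or about 1-17.5% at -0.10 to -0.20, follows only from the assumed burdens and volumes. The textual finding does not depend on those figures. The DLT rule, which concerns interruptions begun before day 14, and the week-2 quantitative change are unaffected.

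**What to change.** - **6.3.22:** make CSF collection at weeks 4 to 10 mandatory for participants *whose previous qualitative or quantitative culture was positive*.
- **One definition:** a negative CSF culture means that the qualitative and quantitative cultures of the same sample are both negative after 2 weeks of incubation. Apply it in the Schema, 3.0, 4.5.1, 4.5.3, 6.1 and 6.2.2.
- **Week-10 failure:** count failure if either culture of the week-10 sample is positive, and align the wording in the Schema, 3.0 and 5.1.1.

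If a quantitative-only rule is intended, the protocol should say so in each of these places and justify it.

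The cost is wording in the amendment that already has to be made before Stage 2. Discordant participants would have further lumbar punctures at visits already scheduled, and some would stay longer on high-dose fluconazole with its toxicity risk. On the illustrative -0.10 to -0.20 rows that is about 0.3 to 4 of 24 per Stage 2 fluconazole arm after the week-2 sample. The sample size does not change.
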